### **Background and Purpose:**

Radiotherapy (RT) is an important modality to treat head and neck (H & N) cancer. Only a few studies have reported that smell function deteriorated in H & N cancer patients after RT. But how long does the olfactory disorder appear after RT? What is the relationship with radiation dose and field? Could it be restored? If yes, how long is the recovery time? There is currently no research to fully explore those important issues. In addition, there are obvious differences in the familiarity of olfactory samples between different races. Westerners' olfactory assessment tools might not be suitable for accurate evaluations of the variations in olfaction of Taiwanese H & N cancer patients before and after treatments. Currently, an available olfactory assessment tool has been developed specifically for Taiwanese people. Therefore, in order to comprehensively evaluate the olfactory function of patients with H & N cancer patients after receiving intensity-modulated radiotherapy (IMRT), we initiated this prospective longitudinal study. This study will investigate the time, degree and prognosis of olfactory disorders in the acute and chronic phases after RT treatments.

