### Lack of the past researches

There were fewer studies investigating the effect of RT on the sense of smell in patients with H

& N cancer, compared with the complications of oral cavity, such as gustatory function and mucositis. Therefore, it lacks several important information about RT-associated dysosmia, such as how long does it take to develop smell impairments after radiation? How is the degree of impact related to the dose and field of radiotherapy? Could the olfactory dysfunction recover? and how long will it take to recover? Therefore, we conduct this prospective study to explore these important issues in radiation induced smell impairments.

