### **Time points of evaluation**

The time points for olfactory-associated assessments in the study include 1. before IMRT, 2. at the time of IMRT completed, 3. 1, 3, 6, and 12 months after IMRT. At each time points, the results of examination will be labelled as “primary assessment”. However, if sinusitis is noted at the primary assessment, adequate treatment will be given, and an intact evaluation will be repeated if the sinusitis is completely resolved. The results of repeated evaluation will be labelled as “secondary assessment”.

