### Scoring method

The scoring method of the olfactory testing device is explained as follows:

1. Zone A: 1 point for correct, 0 point for wrong.
2. Zone B: 0 point for "guess", 1 point for "smell but not sure", 2 points for "did smell".

**Note 1:** Zone A fills in error and zone B fills in "smell but not sure" to get 1 point.

**Note 2:** Zone A fills in error and zone B fills in "did smell" to get 0 point.

The testing book has a total of 16 questions; the maximum score for the zone A is 16 points, and the maximum for the zone B is 32 points. Summing the scores of zone A and B gets a full score of 48 points. According to the score, it can be judged that the sense of smell is *normal*, *hyposmia*, or *anosmia*.

| Age / Olfactory status | Anosmia     | Hyposmia     | Normal       |
|------------------------|-------------|--------------|--------------|
| 20-35 years old        | 0-11 points | 12-43 points | 44-48 points |
| 36-55 years old        | 0-11 points | 12-42 points | 44-48 points |
| 56-80 years old        | 0-11 points | 12-39 points | 40-48 points |

**Note:** The results of examinations under 19 years of age are interpreted according to the standard of 20-35 years; results of persons over 81 years of age are interpreted according to the standard of 56-80 years old.

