### **Statistical analysis**

The sample size was based on a power of 80%. Using a two-tailed *t* test with  $p < 0.05$ , we

estimated the sample size as 60 participants, with an allowance for a potential dropout rate of 20%. The demographic characteristic and comorbidities of those H & N cancer cases are described as mean with standard deviation. Student *t* test will be used to analyze the variation of TW-SIT scores and the results would be plotted as multiple sloping chart. All data were analyzed using Microsoft Excel and MedCalc statistical software. A *p* value of <0.05 was considered statistically significant.

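### The protocol asks when smell loss appears, whether it recovers and how long recovery takes, but the only inferential method it fixes for smell is a t test of mean scores, which gives no proportion with onset or recovery

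*Protocol*

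**What the plan says.** **The questions.** Background and Purpose asks how soon the disorder appears, how it relates to dose and field, whether it can be reversed and "If yes, how long is the recovery time". It then commits the study: "This study will investigate the time, degree and prognosis of olfactory disorders in the acute and chronic phases after RT treatments". The section on the lack of past research gives the same questions as the reason for the study: "how long does it take to develop smell impairments after radiation", and "Could the olfactory dysfunction recover? and how long will it take to recover".

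**The measurements.** TWSIT is given before IMRT, at its end, and at "1, 3, 6, and 12 months after IMRT". Under Scoring method the total score is also turned into a category: "it can be judged that the sense of smell is" normal, hyposmia or anosmia, with cut-offs by age band.

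**The analysis.** In Statistical analysis, the Student t test "will be used to analyze the variation of TW-SIT scores and the results would be plotted as multiple sloping chart", with significance at p<0.05. The section does not say whether the test is paired or which visits are compared. It does not use the three categories, and it has no criterion for onset or recovery.

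**The concern.** Whether smell loss occurs, whether it recovers and over what time are questions about how many patients change state and between which visits. A t test of scores answers a different one: does the mean differ between two visits? A mean can be close to baseline while a minority remain impaired, and it can be low because a few patients lost a great deal.

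The section fixes no other inference on smell. A reader looking for a statement about recovery would therefore have little beyond a later visit at which the mean no longer differs significantly from baseline. That result depends on how many patients remain as well as on their sense of smell. At stake is whether the report answers the questions the protocol poses, although the data to answer them will have been collected.

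**Working it through.** **1. Question against method.**

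| Question in the protocol | What a t test of scores gives |
|---|---|
| When does smell loss appear? | Scheduled visits at which the mean differs from baseline; no proportion affected |
| Can it recover? | Whether a late mean still differs; no proportion recovered |
| How long does recovery take? | At best, the visit at which the difference stops being significant |

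**2. The plan's own figure.** Statistical analysis gives 60 participants for 80% power, a two-tailed t test at 0.05 and a 20% dropout allowance. It states no effect size or SD, so 60 cannot be reproduced. Working backwards:
- 60 × (1 − 0.20) = 48 evaluable. A paired t test then has 80% power for a mean change of 0.41 SD of the change.
- The Patients section plans 100. 100 × (1 − 0.20) = 80 evaluable, and the detectable change is 0.32 SD.

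**3. What a non-significant late visit would mean.** Assume a true mean deficit of d (in SDs of the change score) persists at that visit. For a two-sided paired test at 0.05,

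P(non-significant) = F(t; n−1, d√n) − F(−t; n−1, d√n),

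where F is the noncentral t distribution function and t is the 97.5% point of the central t on n−1 degrees of freedom.

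- n = 48, d = 0.3: t = 2.012, d√n = 2.078, probability 0.470.
- n = 80, d = 0.3: t = 1.990, d√n = 2.683, probability 0.245.

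| Persisting deficit (assumed) | n = 48 | n = 80 |
|---|---|---|
| 0.2 SD | 73% | 58% |
| 0.3 SD | 47% | 24% |
| 0.4 SD | 23% | 6% |

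The deficit is the same along each row. Only the number of patients differs, so losing patients makes a non-significant result more likely. These are paired figures; the protocol does not say that the test is paired.

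**4. Whether the categories can carry the missing analysis.** They can, once three points are settled.
- The Patients section excludes anosmia but not hyposmia. Patients hyposmic at baseline cannot newly become hyposmic, so onset needs patients normal at baseline as its denominator.
- In the Scoring method table, ages 36-55 have hyposmia at 12-42 and normal at 44-48. A score of 43 has no category.
- A score of 41 is hyposmia at age 55 and normal at 56, so a birthday during follow-up could change the category with no change in score.

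Time points of evaluation also creates a primary assessment at each visit and a secondary one after sinusitis has resolved, so the analysis must say which is used.

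**5. Precision of a proportion.** Near 50%, the 95% half-width is 1.96 × √(0.25/n): ±14 percentage points with 48 patients and ±20 with 24.

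**The case against.** The strongest reply has four parts.

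- **The questions are background, and the operative aim is broader.** Specific aim 1 speaks of effect and prognosis, and the first-year plan of a trend before and after IMRT. A group-level reading is possible, and under it comparisons by visit and the chart do bear on timing, though crudely. This stands, so it goes too far to say that the stated analysis has no bearing on timing. It does not supply the proportions affected and recovered, and the commitment to study time and prognosis is in the protocol's own statement of purpose.
- **Event definitions can be left to an SAP.** True of many details, and no SAP is at hand. The point here is that the protocol names a method, and the method does not match the question.
- **The protocol does not misuse non-significance.** A reader might infer that the trial will call a non-significant difference recovery. No section says so. The probabilities above show why such a result would not be evidence of recovery; they do not describe a rule in the plan.
- **The protocol does not date events at visits.** A reader might also infer that recovery times will be overstated because recovery is dated at the visit where it is first seen. No dating rule is stated, so that bias cannot be charged to the plan.

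A formal interval-censored estimator is also tempting as a remedy. All patients share one visit grid, so it would add little to proportions by visit. With time counted from the end of IMRT, onset first seen at that visit would have a lower bound before time zero.

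**Conclusion.** The point holds as a mismatch between stated questions and stated method. For smell, the fixed inference is a t test of scores. It gives no proportion with onset or recovery, and no timing beyond the visits at which means differ.

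Under an assumed persisting deficit of 0.3 SD of the change, a paired test would miss it with probability about 47% at n = 48 and 24% at n = 80. Over deficits of 0.2 to 0.4 SD the range is 73% to 23% and 58% to 6%. These figures rest on the assumed deficit, on pairing and on 20% loss from 60 or 100 patients.

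A reader might conclude that the trial cannot answer its questions. The documents do not support that: scores are collected at all six time points and can be categorised, so the gap is in the analysis and can be closed without new data. The change should be made before the data are analysed.

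**What to change.** In Statistical analysis, keep the score analysis and report the mean change from baseline at each visit with its 95% CI. Then add:

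1. **Onset.** Among patients normal at baseline, the proportion in a worse TWSIT category at the end of IMRT and at 1, 3, 6 and 12 months, each with a 95% CI.
2. **Recovery.** Among patients with onset, the proportion back in the baseline category at each later visit, with a 95% CI. Report timing as the interval between two visits, not as an exact date.
3. **Ground rules.** Fix the age band at baseline age. Reconcile the unclassified score of 43 at ages 36-55 before the categories are used. Analyse the primary assessments, and repeat the analysis with the secondary assessments made after sinusitis has resolved.
4. **Interpretation.** State that a non-significant mean difference from baseline is not evidence of recovery.

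The cost is a few sentences and modest analysis work, with no new visits or patients. There are three drawbacks. Categories use less information than scores. A small change near a cut-off can change the category: at ages 20-35, 44 is normal and 43 is hyposmia. The intervals will be wide if few patients have onset. Keeping the score analysis beside the proportions limits the first two.

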### **Methods:**

The research population of this study is newly diagnosed H & N cancer patients who receive curative IMRT at Chiayi Chang Gung Memorial Hospital during the study period. It is estimated that 100 patients will be enrolled in three years. Before RT, at the end of RT, one month, three months, six months and one year after RT, those patients will be tested by the Taiwan version of the olfactory assessment tool to evaluate their olfactory status. In addition, the Taiwan version of Sino-nasal Outcome Test-22 will be used to assess the subjective nasal symptoms of those H & N cancer patients. Nasal endoscopy will be performed to investigate and record the state of the nasal cavity of them, and we will collect those patients' nasal secretions for testing to analyze the changes in the nasal microenvironment.

Keywords : Loss of smell, Olfactory dysfunction, Hyposomnia, Anosmia, head and neck cancer, radiotherapy, IMRT

Please provide an overview of the anticipated impacts that the implementation of this project may have on various aspects, including social, economic, and academic development, in no more than 150 words.

Loss of smell can reduce the quality of life, sometimes cause danger, such as inability to smell harmful substances, and reduce the taste of food and cause nutritional disorders. Based on the findings of this study, we can comprehensively realize the effect and prognosis of RT on the olfactory function in H & N cancer patients. Then, on the basis of this research, we will have the opportunity to research and develop effective therapies for preventing, attenuating or treating the radiation-associated complication.

## Backgrounds & Purpose:

### Common radiotherapy complications

Radiotherapy (RT) is an important method to treat Head and Neck (H & N) cancer patients. The area of the head and neck receiving RT often leads to complications of varying degrees, such as xerostomia, dental problems, taste disorders, mucositis, etc. These problems can cause malnutrition in patients and seriously affect the quality of life.

### Radiation-associated olfactory dysfunction

The endings of the olfactory nerve are located on the olfactory epithelium and bulb where the junction of the nasal cavity and anterior skull base, which is generally called the cribriform plate. It is close to the nasopharynx and easily falls into the scope of radiotherapy for treating H & N cancer. Although there were few studies discussing on the alternation in the sense of smell of patients with H & N cancer after RT, sporadic studies have reported that these patients would have olfactory dysfunction after treatment. Veyseller *et al* used Connecticut Chemosensory Clinical Research Center (CCCRC) test, a commonly used tool for accessing olfactory function, to evaluate the changes of smell in 24 Nasopharyngeal cancer (NPC) cases after RT. The mean CCCRC score was  $5.5 \pm 1.1$  for those NPC patients and  $6.4 \pm 0.4$  for a control group, which indicated a significant reduction in the olfactory function ( $p = 0.003$ ).

The perception of smell plays an important role in daily life, for example, it can avoid inhaling harmful substances, which would cause damage of the respiratory system. In addition, the sense of smell is also related to the perception of taste. Dysfunction of smell would deteriorate radiation-induced taste disorders, which could reduce appetite and affect the nutritional status of NPC patients.

### Lack of the past researches

There were fewer studies investigating the effect of RT on the sense of smell in patients with H

& N cancer, compared with the complications of oral cavity, such as gustatory function and mucositis. Therefore, it lacks several important information about RT-associated dysosmia, such as how long does it take to develop smell impairments after radiation? How is the degree of impact related to the dose and field of radiotherapy? Could the olfactory dysfunction recover? and how long will it take to recover? Therefore, we conduct this prospective study to explore these important issues in radiation induced smell impairments.

### **Common tools for testing smell function**

At present, the following tools are mainly used for olfactory detection in the world, including the University of Pennsylvania Smell Identification Test (UPSIT)  and the Connecticut Chemosensory Clinical Research Center identification test (CCCRC)  in the Unites States, and the Sniffin Sticks test in Europe .

### **Odor familiarity**

Regarding the choice of an adequate tool for the odor identification test, the most important factor is whether the tested race is familiar with the types of smell used in the detection tool. For example, a certain smell in an odor identification test is quite familiar to one race, but this smell may be unfamiliar to another race, and herein, the tool is not suitable for the latter.

For Orientals' olfactory testing, the Traditional Chinese version of UPSIT (TC-UPSIT) is currently commonly used , but the flavors used in the test are still based on things familiar to Westerners, such as the odors of pizza, motor oil, strawberry and chocolate, but these odors might not be familiar to Taiwanese people (or even Asians).

### **Specific olfactory assessment for Taiwanese – “TWSIT”**

H & N cancer is a common cancer in Taiwan and compared with other countries in the world,

the prevalence of H & N cancer in Taiwan is relatively high. Therefore, it is suitable and feasible to collect enough H & N cancer cases in Taiwan to investigate the effect and prognosis of RT-associated olfactory dysfunction. However, as described in the previous paragraph, only by choosing an appropriate tool for smell evaluation can obtain the accurate outcomes. Therefore, a designed odor identification test based on the smells familiar to Taiwanese is the most suitable tool for studying the issue.

A brief and reliable smell identification test named the Taiwan Smell Identification Test (TWSIT) was developed and available currently. The test includes a novel questionnaire to improve the precision in measuring smell deficits and provides clinicians with a convenient, validated, measure of olfactory function in Taiwanese patients.

### **Effects of sinusitis on olfaction**

Past studies have also pointed out that sinusitis itself could cause olfactory dysfunction. But the sinusitis-related smell impairment is probably the most treatable form of olfactory dysfunction. Most studies reported that the effects are usually transient and incomplete.

Patients with H & N cancer, especially NPC, was found to be prone to develop sinusitis during and after radiotherapy. Su et al studied 155 NPC cases without sinusitis before RT and found the incidence rates of sinusitis at the end of RT and at 1, 3, 6, 9, 12, and 18 months after RT were 32.9, 43.2, 61.3, 68.4, 73.5, 69.7, and 61.3 %, respectively. The occurrence of sinusitis increased rapidly within the first 3 months after IMRT, and the number of sinusitis cases peaked at 6-9 months after IMRT and showed a trend toward stabilization after 1 year.

In the past studies on discussing the effect of RT on smell in NPC patients, they only excluded NPC cases with chronic sinusitis before enrolling process, but no research evaluated the effect of sinusitis developing during and after radiotherapy on confounding the assessments of radiotherapy-associated olfactory alternation.

## **Olfactory disorders and nasal microenvironment**

The plasma levels of interferon- $\gamma$  (IFN- $\gamma$ ), interleukin (IL)-1b, IL-6, monocyte chemoattractant protein (MCP-1), tumor necrosis factor (TNF)- $\alpha$ , IL-2 and IL-5 were reported to be significantly increased in NPC patients and dramatically decreased after treatment. But few studies investigating the cytokines in the nasal secretion before and after NPC treatment.

Whether the changes of cytokines in the nasal microenvironment have correlation with the alternation of olfactory function, which is worthy of research and the understanding of the relationship might provide clues to develop methods for preventing, attenuating or treating the radiotherapy-associated olfactory dysfunction.

## Materials & Methods:

**Specific aim 1:** Evaluating the effect and prognosis of IMRT on the olfactory function in H & N cancer patients by using a smell identification tool designed for Taiwanese.

### Patients

This study will enroll 100 patients initially diagnosed with H & N cancer at the Chiayi branch of Chang Gung Memorial Hospital in three years. The inclusion criteria include 1. patients should be older than 20 years old, 2. the H & N cancer treatments should contain IMRT, and 3. they should be willing to sign an informed consent approved by the institutional review board. The exclusion criteria include 1. patients with severe olfactory dysfunction (anosmia) and 2. patients with sinusitis before H & N cancer treatment.

**# Note 1:** we will apply TWSIT to screen patient's olfactory state and if the result is anosmia, the patient will be excluded.

**# Note 2:** If a patient is found to have sinusitis before treatment for H & N cancer, but if the sinusitis is completely resolved after adequate treatment before IMRT, the patient can still be included in this study.

### Basic data

Before this trial, these enrolled patients will be recorded: 1. age and gender, 2. TNM, stage and images of their H & N cancer, planned dose and field of IMRT, 3. if having a habit of smoking, 4. if having the following medical comorbidities, including diabetes mellitus, hypertension, heart disease, chronic kidney disease, autoimmune disease, liver cirrhosis, chronic obstructive pulmonary disease, and 5. whether having received nasal turbinate, septum or sinus surgery.

### **Time points of evaluation**

The time points for olfactory-associated assessments in the study include 1. before IMRT, 2. at the time of IMRT completed, 3. 1, 3, 6, and 12 months after IMRT. At each time points, the results of examination will be labelled as “primary assessment”. However, if sinusitis is noted at the primary assessment, adequate treatment will be given, and an intact evaluation will be repeated if the sinusitis is completely resolved. The results of repeated evaluation will be labelled as “secondary assessment”.

### **Evaluation content**

The olfactory-associated assessments applied at each time points include 1. Taiwan version of smell identification test (TWSIT), 2. Sino-nasal Outcome Test -22 (SNOT-22), 3. nasal endoscopy, 4. collection of nasal secretions for cytokine analysis. The following describes the details of these detection methods in order.

